### 2.5. Participants

Participants have to meet the following inclusion criteria: (1) to be aged between 8 and 16 years old; (2) to be registered and/or residing in Portugal; (3) not suffer from pathologies that contraindicate exercise practice, limit the execution of the PA programme or require special attention; (4) to be authorised by parents or legal guardians; and (5) to participate in the study.

### 2.6. Intervention

Experimental group: A 3-month physical active breaks intervention will be carried out in the educational centres during break times, with a frequency of three times per week. The duration of each session will be between 20 min, based on the time pre-established by each educational centre for the students’ break.

Specifically, in order to develop the domains that make up physical literacy, the PLBreaks programme will consist of two blocks of 10 min. Both blocks will favour the development of physical competence through different physical activities. In addition, the first block will be focused on the acquisition of knowledge and healthy life habits that will contribute to the development of the domains of knowledge and understanding and daily activity. Finally, the second block, in addition to favouring physical competence, will try to improve motivation through different strategies that will be detailed below. 

In the first block, activities will be carried out to develop the knowledge and understanding of concepts and attitudes related to physical activity (Figure 1). This will be performed with the following activities:Find the question: Participants, in pairs, will have a map with different points marked on it (beacons). They will have to find the maximum number of beacons and answer the questions that are exposed in these points on a record sheet.Body performances: Participants in groups will have to act out the content of the week through body movements and their partners will have to guess their actions. Card relay race: Participants will be divided into teams, which will be placed in rows. Each participant of each team will have to run individually to a table located about 30 metres away, and once there, they will find a series of cards, and will have to place the card they will be holding on their corresponding (partner) and return to the end of the line for the next participant to come out. 

The second block will be based on active play, as it is fundamental in the transmission of values and attitudinal content as well as stimulating social and civic relations with others [29]. Similarly to previous studies [30,31], for this study, the proposed Ontario Physical and Health Education Association’s PlaySport activities (http://www.playsport.net/ (accessed on 20 May 2022)) will be used (Figure 1). During the games, basic skills will be developed, such as moving, jumping, spinning or throwing, thus trying to improve them as well as the children’s motivation. The games will have a cooperative and competitive component due to the motivational benefits this can bring [32]. The activities will be adapted to the initial level of the children’s.

Specifically, during the second block, in order to improve the motivation and confidence of the participants, some strategies should be fulfilled. In this regard, participants’ inclusion will be ensured during all activities (both by gender and ability) by adapting all activities so that all participants can learn and participate actively. Furthermore, to satisfy the need for peer relationships, strategies will be used in group formation and cooperative activities with a common goal that participants will have to achieve together. [33]. In addition, activity coordinators and children will be encouraged to provide verbal feedback to participants in order to ensure active participations, fostering relation-inferred self-efficacy (RISE) [30,34]. Finally, they will be provided time at the end of each session to express their opinions [33].

**Figure 1 biology-11-00910-f001:**
[figure not shown]
Activities and contents to be developed during the PLBreaks programme.

Control group: Participants will continue with their normal daily routine during school breaks (interacting among peers and playing freely or eating their snacks), which will not include any physical exercise similar to the exercise practiced by the experimental group.

### 2.7. Measures

A variety of tools will be used to assess the PL and body composition of schoolchildren. Before the first measurement, all participants will undergo a familiarisation phase to become acquainted with the different instruments and assessments included in this project.

a.Anthropometric and body composition measurements:

Height, bodyweight, fat mass and fat-free mass will be taken at baseline at the end of the intervention (month 4) and one month after the end of the intervention (follow-up).

Anthropometric measurements will be taken under standardised conditions and following WHO recommendations for the development of the Childhood Obesity Surveillance Initiative (COSI) [35]. Before starting any of the measurements, participants will be asked to remove their shoes and socks, as well as any heavy clothing (coats, jumpers, jackets, etc.). They will also be asked to empty their pockets and remove their belts and any other accessory (headbands, pendants, etc.). 

Height shall be measured with a measuring rod (Tanita Tantois, Tanita Corporation, Tokyo, Japan). The instrument shall be placed on a vertical surface with the measuring scale perpendicular to the ground. Participants will be positioned on a standing position, with the shoulders balanced and the arms relaxed along their body. The head will be held in the Frankfurt plane. Height will be taken in cm and rounded to the nearest mm. 

Bodyweight will be measured using a bioimpedancemeter (Tanita MC-780 MA, Tanita Corporation, Tokyo, Japan). The assessment shall be performed in ‘standard mode’ by entering the participant’s age, sex and height. Bodyweight will be recorded in kg, with an accuracy of 100 g. This instrument will also be used to assess participants’ fat mass, fat mass percentage and fat-free mass. To obtain accurate measurements from the bioimpedancemeter, preconditions will be standardised according to the manufacturer’s guidelines [36,37]: (a) more than 3 h after waking up; (b) urinating before the measurement; (c) not eating or drinking within the last 3 h; (d) not eating or drinking excessively the previous day; (e) no vigorous exercise within the last 12 h; (f) no alcohol consumption within the last 12 h; and (g) no use of metal objects or wearing a pacemaker.

BMI will be determined using the following formula: weight × height^−2^. The criteria of the COSI initiative [35] and WHO growth standards [38] will be used to establish weight categories. Participants’ weight status will be established based on the standard deviation (SD) criteria: (1) <−3 SD, “underweight”; (2) <−2 SD, “normal weight”; (3) >+1 SD, “overweight”; and (4) >+2 SD, “obese”. 

b.Physical Literacy:

The level of PL will be assessed at the beginning, at the end of the intervention and one month after the end of the programme by applying the Canadian Assessment of Physical Literacy Development (CAPL-2) [39]. This assessment includes 4 domains: (1) daily physical activity behaviour, (2) physical competence, (3) motivation and confidence and (4) knowledge and understanding. Each domain will consist of a score and different tests. 

Every domain comprises CAPL-2 and the methods detailing how they will be scored are described below.

Daily activity behaviour. The total score will be calculated from two components: step counts obtained using an activity wristband (Xiaomi mi Band 3, Xiaomi Corporation, Beijing, China). These wristbands will record steps for a full week, and a self-reported question on the number of days active for at least 60 min. The total score for this domain will be composed of the score based on the number of steps recorded and the score assigned to the response to the self-reported question on the number of minutes of weekly activity.

Physical competence. The final score for this domain will be reached by the sum of the scores of three components: -*Plank* [40], which consists of maintaining the plank position for as long as possible;-*Progressive Aerobic Cardiovascular Endurance Run* (PACER) test [41], which will allow the measure of cardiorespiratory competence, using a 20 m running test (out and back), following an acoustic signal that determined the intensity of each test stage;-*Canadian Agility and Movement Skill Assessment* (CAMSA) [42], which will test the motor skills of participants through an agility circuit, including throwing, jumping and moving actions.

All tests will be evaluated with a possible score from 1 to 10 points. Thus, a total score of 30 points can be obtained for this domain.

Motivation and confidence. It will be assessed by using the CAPL-2 motivation and confidence questionnaire [39]. It will assess participants’ confidence in the ability to be physically active and motivation to participate in PA. The score will be obtained by the sum of four different dimensions assessed from 1 to 7.5 points: intrinsic motivation, competition, predilection and adequacy. The total score for the domain will be between 1 and 30 points. 

Knowledge and understanding. This domain will assess knowledge about PA [43]. Its score will be obtained from the questionnaire included in the CAPL-2 manual, which includes five questions, four of which are multiple-choice questions and will be scored from 0 to 1. The last question will consist of filling in missing gaps to complete a story and it will be scored from 1 to 6.

Finally, the numerical scores for CAPL-2 will be between 0 and 100 points. Based on these scores, participants will be classified into four levels by considering their sex and age: “insufficient”, “in progress”, “sufficient” and “excellent”. The “insufficient” and “in progress” levels will correspond to children who have not yet reached the optimal level of PL. The “sufficient” level will correspond to children who have reached a score associated with sufficient PL. Finally, the “excellent” level will demonstrate a high level of PL.

### 2.8. Statistical Analysis

Descriptive statistics and computations will be performed with SPSS (version 25.0; IBM SPSS Inc., Armonk, IL, USA). Data will be presented as means and standard deviation (SD).

The normality and homogeneity of data will be checked applying Kolmogorov–Smirnov and Levene’s test, respectively. Then, a repeated measures ANCOVA will be applied to analyse the intervention effects on the different dependent variables, adjusted by age and baseline outcomes. Cohen’s d (with 95% confidence interval) will be also included in the results as the effect size. Effect sizes thresholds will be interpreted as follow: >0.2, small; >0.5, moderate; >0.8, large [27]. Statistical significance will be computed for the effect of time and the interaction group × time. Alpha level will be fixed at *p* ≤ 0.05.

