In Portugal, only one study [25] related to PL has been found, which aimed to validate a battery for its evaluation. However, this battery was focused on adolescents aged between 15 and 18 years; thus, there are currently no studies that evaluated PL in children and no studies that have developed programmes aimed at improving PL. Despite this, we consider this multidimensional assessment and intervention model to be of great interest. 

Thus, this study aimed to (1) evaluate the effectiveness of the Physical Literacy Breaks (PLBreaks) programme on schoolchildren’s PL (general PA, physical competence, motivation and knowledge domains) and (2) evaluate the effectiveness of the PLBreaks on children’s body composition.

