### 2.3. Sample Size

Sample size computations were conducted by using G*Power software 3.1.9.4 (Kiel University, Kiel, Germany) and selecting the statistical test to compare the difference between two independent means (two groups). Thus, accepting a 0.05 alpha risk and a 0.2 beta risk in a bilateral contrast and assuming a moderate effect size of 0.5 [27], a total of 128 participants (64 subjects in the experimental group and 64 in the control group) were sufficient for achieving a minimum power of 80%. 

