## 4. Conclusions

The present study will investigate the efficacy of PLBreaks in schoolchildren to improve their PL and body composition. If the efficacy of the program is demonstrated, it can be implemented in schools.

Therefore, the main added value of this study is the acquisition of new knowledge concerning PL from an immediate perspective of practical and direct application. It will represent a scientific advance in terms of improvement and adherence to health-related PA, as well as the prevention of diseases associated with physical inactivity such as overweight and obesity.

On the other hand, the PLBreaks could be the response for solutions to a social problem such as the difficulties of access in many cases (due to socio-economic reasons) to PA programmes that are related to health. Thus, given that it is a low-cost programme that can be easily standardised by levels of difficulty (adapting to the different levels of PA), its transfer and implementation would not be a problem in the public sphere, and it includes the possibility of including the intervention in public education programmes.

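### No outcome or time point is named as primary and the sample size is tied to none, so the stated 5% alpha and 80% power belong to no identified efficacy claim

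*Protocol article*

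**What the plan says.** **Aims (section 1).** The first aim is to "evaluate the effectiveness of the Physical Literacy Breaks (PLBreaks) programme on schoolchildren’s PL (general PA, physical competence, motivation and knowledge domains". The second is the programme's effect on body composition. Neither is ranked above the other.

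**Sample size (section 2.3).** The calculation was done by "selecting the statistical test to compare the difference between two independent means (two groups", "accepting a 0.05 alpha risk and a 0.2 beta risk in a bilateral contrast" and "assuming a moderate effect size of 0.5". The result is "a total of 128 participants (64 subjects in the experimental group and 64 in the control group". No outcome is attached to the effect size.

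**Visits (section 2.1).** Both groups are assessed at baseline, at the end of the programme and one month later.

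**Analysis (section 2.8).** A repeated measures ANCOVA, adjusted for age and baseline, will "analyse the intervention effects on the different dependent variables". Tests of time and of group × time are reported. "Alpha level will be fixed at" p ≤ 0.05. Cohen's d is given with a 95% confidence interval.

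**Use of the result (section 4).** "If the efficacy of the program is demonstrated, it can be implemented in schools". No section says which result would demonstrate efficacy.

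**The concern.** An alpha of 5% and a power of 80% describe one hypothesis test. Section 2.3 gives both figures but not the hypothesis. Section 2.8 then applies the 0.05 threshold to a set of variables without ranking them, and without saying which of the two post-baseline visits, or which contrast, counts.

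The efficacy conclusion could therefore rest on whichever domain score or body composition variable happens to cross 0.05, and it would not carry the 5% error rate that the protocol states. The time effect adds to the room for selection: it is not a comparison between groups and cannot show efficacy, yet its significance is reported beside the interaction. What is at stake is the trial's central claim, on which the protocol would base use in schools.

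**Working it through.** **1. The plan's own figure.** Inputs from section 2.3: two-sided alpha 0.05, power 0.80, d = 0.5, two independent means, equal groups. The noncentral t calculation gives n = 63.77 per group, rounded up to 64, so 2 × 64 = 128. Power at 64 per group is 80.1%. The stated N is reproduced and is correct for one comparison.

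**2. How many outcomes.** Section 2.8 gives no list, so it has to be rebuilt from section 2.7:
- Physical literacy: CAPL-2 total and four domains = 5.
- Body composition: height, bodyweight, fat mass, fat mass percentage, fat-free mass and BMI = 6.
- Sum: 5 + 6 = 11. Without fat mass percentage and BMI, which are not in the opening list of section 2.7, it is 9. It would be more than 11 if the component tests were analysed separately.

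**3. At least one false-positive group × time result under no effect, independent tests.** Formula: 1 − 0.95^m.
- m = 9: 1 − 0.95^9 = 37.0%
- m = 11: 1 − 0.95^11 = 43.1%

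Independence is the upper reference. These outcomes are linked: the CAPL-2 total is built from its domains, and BMI is computed from weight and height.

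**4. Correlated tests, m = 11.** The documents give no correlations, so these are assumptions. Test statistics are taken as normal with equal pairwise correlation ρ, and each is treated as a two-group contrast. The favourable column counts only results in the programme's favour, at 0.025 per test.

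| ρ (assumed) | Either direction | Favouring the programme |
|---|---|---|
| 0 | 43% | 24% (1 − 0.975^11) |
| 0.3 | 37% | 19% |
| 0.5 | 30% | 15% |
| 0.7 | 22% | 11% |

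For a single test the matching nominal rates are 5% and 2.5%.

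**5. Check with a more realistic structure.** Assume domains correlated at 0.2–0.5, the total as the sum of the domains, body composition variables correlated at 0.6–0.9, and 0–0.3 between the two sets. The either-direction figure is then 24–34%, inside the range in step 4.

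**6. One pre-specified primary test.** Type I error is 5% two-sided and power is 80.1% at d = 0.5 with 64 per group. N stays at 128 as far as this point is concerned.

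**The case against.** **The any-one-outcome rule is not in the text.** This is correct. Section 4 speaks of improving physical literacy and body composition, which could mean that both must succeed. That reading does not rescue the stated figures: two outcomes each powered at 80% give 0.80 × 0.80 = 64% joint power if independent. On either reading, alpha and power are attached to no named claim.

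**The list of outcomes is a reconstruction.** Also correct. A reader might infer that the plan tests height for efficacy. The documents do not support that: height is measured, but it is also an input to the bioimpedance device and to BMI, and being measured is not the same as being tested. The count is therefore given as about 9 to 11.

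**43% overstates the risk.** It does if taken as the trial's actual error rate. It needs independent tests, which these are not, and it counts results in both directions. The lower figures apply to a wrong claim of benefit, and they still exceed 2.5% several times over.

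**A multiplicity method may sit in a statistical analysis plan.** It may, and its absence here is not held against the protocol. However, the article reports a completed sample size calculation and a decision threshold. The outcome that these serve is a protocol matter, and sections 2.3, 2.7 and 2.8 do not name it.

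**Conclusion.** The point stands. The protocol fixes a threshold and a sample size without naming the outcome, visit or contrast to which they apply, so its 5% and 80% belong to no identified efficacy claim.

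The size depends on reading any single significant group × time result as efficacy, which the text permits but does not state. On that reading the chance of at least one false-positive result is at most 37–43% for 9 to 11 outcomes. For 11 outcomes it is about 22–37% under assumed correlations of 0.7 to 0.3, of which 11–19% would favour the programme against a nominal 2.5%.

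A reader might also infer that 128 children are too few. The documents do not support that on this ground: the number is right for one comparison, and what is missing is the name of that comparison. The point should be settled before data are analysed, because choosing the primary outcome after seeing results cannot restore error control.

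**What to change.** Before data are analysed, state in sections 2.3 and 2.8:
- one primary outcome, one time point and the contrast that supplies its p-value. An example is the between-group difference in CAPL-2 total score at the end of the intervention, adjusted for baseline and age, at two-sided 0.05. The choice is the sponsor's, not least because the first aim lists the four domains and not the total;
- that the 128 participants and 80% power at d = 0.5 refer to that comparison;
- that the remaining physical literacy scores and body composition are secondary, reported as estimates with 95% confidence intervals, and not sufficient alone for an efficacy claim.

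Tie the efficacy statements in the abstract and section 4 to the primary outcome.

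**Cost.** No added participants or measurements. The change is more than wording in one respect: two parallel aims become ranked, and the sponsor has to accept that. A significant result on a single domain or body composition variable will no longer support an efficacy claim by itself.

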## 3. Discussion

A great interest in the concept of PL is emerging due to its comprehensive character on the development of physical activity. Several studies have started to evaluate and design intervention programmes based on it [30,31,44,45]. However, most of them are focused on some of the domains that comprised PL and not overall. Moreover, most programmes have been carried out within physical education classes [44,45] or in out-of-school settings [30,31]. This project would be the first to implement a programme to develop PL during the break period of the school day and, to the best of our knowledge, the first in Portugal to assess PL in children. 

In Portugal, around 35% of Portuguese people over 14 years old never or rarely take active breaks (e.g., walking, standing or jogging) during sitting time [6]. Break times may be an ideal time for the development of PL, as it has been shown that education and health interventions can improve the physical fitness and health of their participants [22]. In addition, this intervention would contribute towards meeting the World Health Organisation’s physical activity recommendations, which state that children aged 5–17 years should engage in at least 60 min of Moderate to Vigorous Physical Activity (MVPA) per day [46]. It has also been shown that the daily steps taken by students participating in an active school break can be increased compared to those who do not [47,48]. This would help fulfil the daily recommendations set out by the President’s Council on Physical Fitness and Sports, recommending 12,000 steps for girls and 15,000 steps for boys [49]. 

All these benefits have recently led to the development of numerous research studies, which implemented active breaks programmes with different objectives based on different activities, such as alternative, popular and traditional games [47]; free play [50]; pre-sports games [51]; and high-intensity interval training (HIIT) [52] o HIIT + intermittent training [53]. However, any previous study has aimed to develop PL into the school context.

Regarding level of PL, several studies have provided results in schoolchildren from different countries [54,55,56,57,58] based on CAPL-2. Most reported worrying results since more than 50% of the schoolchildren participating in these studies did not achieve sufficient PL [54,55,56,58]. 

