Regarding the “knowledge and understanding” domain, previous studies showed that most of the schoolchildren were “in progress” or were “insufficient” [55,56,63]. In this sense, there are hardly any studies that evaluate how knowledge of PA affects subsequent practice. In contrast, other studies that have evaluated how knowledge of certain pathologies affects subsequent treatment have obtained beneficial results [64,65]. Therefore, due to the worrying results reported by the different studies on low knowledge and understanding in this field [54,55,56,58], this study could be very beneficial as an increase in the knowledge about PA could translate into an increase in PL since a relationship has also been found between the two [60]. 

Body composition can have a considerable influence on PL, as several studies have reported significant differences between overweight and non-overweight schoolchildren for the different domains that make up PL [66,67,68,69,70,71,72]. Specifically, in the “daily activity” domain, it has been observed that schoolchildren with obesity performed less daily activity related to physical activity than schoolchildren without obesity [66]. For “physical competence”, it has been shown that overweight schoolchildren have worsened physical competence compared to their normal-weight counterparts [67,68,69,70,71]. In the same line, motivation towards physical activity has been found to be lower in overweight schoolchildren [72]. Regarding the level of knowledge about physical activity, few studies have evaluated this factor in isolation among overweight and obese schoolchildren. However, Nyström, Traversy, Barnes, Chaput, Longmuir and Tremblay [60] reported differences, showing higher knowledge in non-overweight boys. 

Regarding PL and body composition, previous studies have reported a negative correlation between PL and BMI, fat mass [20,58], HRQoL and blood pressure [20]. Nyström, Traversy, Barnes, Chaput, Longmuir and Tremblay [60] and Mendoza-Muñoz, Barrios-Fernández, Adsuar, Pastor-Cisneros, Risco-Gil, García-Gordillo and Carlos-Vivas [58] found that children with a healthy weight scored significantly better on the CAPL than overweight children. Therefore, it can be hypothesised that the development of PL could translate into improved body composition values.

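### The ANCOVA adjusts for age and baseline but leaves out sex, which is recorded and paired with age elsewhere in the article; prespecifying it is a small, nearly free gain in precision, not the repair of an error

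*Protocol article*

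**What the plan says.** Section 2.8 (Statistical Analysis) states that "a repeated measures ANCOVA will be applied to analyse the intervention effects on the different dependent variables", and that the model is "adjusted by age and baseline outcomes". These are the only covariates named.

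Sex appears in several other places:
- Section 2.7 (Measures), body composition: the bioimpedance device is operated "by entering the participant’s age, sex and height", so sex is on file for every child measured.
- Section 2.7 (Measures), physical literacy: once the CAPL-2 total is computed, "participants will be classified into four levels by considering their sex and age".
- Section 3 (Discussion): the article cites a body "recommending 12,000 steps for girls and 15,000 steps for boys", and step count is a component of the daily activity domain. It also cites a study "showing higher knowledge in non-overweight boys".

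Section 2.5 (Participants) requires children "to be aged between 8 and 16 years old". Section 2.4 (Randomisation and Blinding) describes a 1:1 computer-generated sequence and mentions no stratification factor.

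**The concern.** The article names its covariates, so this is a stated choice and not a detail left open. It takes one of two variables that it elsewhere treats as a pair. A given CAPL-2 total is read differently for a boy and for a girl, which means that the raw total is not equated for sex. Yet the raw outcomes are analysed with age in the model and sex out of it.

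Two things could follow. If sex predicts the follow-up value beyond what age and the baseline value already predict, the interval for the group effect is wider than it needs to be. And if the arms differ in sex by chance, part of that difference could remain in the estimated group effect. There is also a point of timing: if sex is added only after an imbalance has been seen, the choice of model becomes data-driven.

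**Working it through.** **Inputs from the article.** 64 children per group, a standardised effect of 0.5, and "accepting a 0.05 alpha risk and a 0.2 beta risk in a bilateral contrast" (Section 2.3, Sample Size). Covariates are age and baseline (Section 2.8).

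**Inputs not in the article, assumed here.** Half the children are girls. The sex gap is dB at baseline and dF at follow-up, in within-sex SD units. The within-sex correlation between baseline and follow-up is r, the same in both sexes. Age is ignored.

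**Step 1: the plan's own figure.** For a two-sided t-test with d = 0.5 and alpha 0.05, the exact noncentral t gives power 79.5% with 63 per group and 80.1% with 64. The stated 128 is reproduced. It rests on an unadjusted comparison of two means and claims no gain from covariates.

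**Step 2: chance imbalance in sex.** The SD of the between-arm difference in the proportion of girls is √(2 × 0.25 / 64) = 0.088. A 1.96 SD imbalance is 1.96 × 0.088 = 0.173, or about 17 percentage points.

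**Step 3: what sex adds once baseline is in the model.**
- Variances: vB = 1 + dB²/4 and vF = 1 + dF²/4. Covariance: c = r + dB·dF/4.
- Residual variance without sex: vF − c²/vB. With sex: 1 − r².
- Partial R² of sex = 1 − (1 − r²)/(vF − c²/vB). Multiplied by 128, this gives the equivalent number of children.
- Sex gap not carried by baseline: dF − (c/vB)·dB. Multiplied by 0.173, this gives the shift in the group contrast at a 17-point imbalance.

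Example with dB = dF = 0.5 and r = 0.5: vB = vF = 1.0625 and c = 0.5625. Residual variance without sex is 1.0625 − 0.5625²/1.0625 = 0.765, and with sex 0.75. Partial R² = 1 − 0.75/0.765 = 1.9%. The remaining gap is 0.5 − 0.529 × 0.5 = 0.235 SD, and the shift is 0.235 × 0.173 = 0.041 SD.

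Results for r = 0.5 / 0.7 / 0.9:

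| Sex gap, baseline → follow-up (SD) | Partial R² of sex | Children out of 128 | Shift at 17-point imbalance (SD) |
|---|---|---|---|
| 0.2 → 0.2 | 0.3 / 0.2 / 0.1% | 0 / 0 / 0 | 0.017 / 0.010 / 0.003 |
| 0.5 → 0.5 | 1.9 / 1.0 / 0.3% | 2 / 1 / 0 | 0.041 / 0.024 / 0.008 |
| 0.8 → 0.8 | 4.4 / 2.4 / 0.7% | 6 / 3 / 1 | 0.060 / 0.036 / 0.012 |
| 0.5 → 0.6 | 3.7 / 2.8 / 2.7% | 5 / 4 / 3 | 0.057 / 0.041 / 0.024 |
| 0.5 → 0.7 | 6.0 / 5.3 / 7.2% | 8 / 7 / 9 | 0.073 / 0.057 / 0.041 |
| 0.8 → 1.0 | 9.4 / 7.6 / 8.2% | 12 / 10 / 10 | 0.090 / 0.066 / 0.042 |

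Without any baseline adjustment, which is not this plan, the shift would be 0.5 × 0.173 = 0.087 SD for a 0.5 SD gap and 0.8 × 0.173 = 0.139 SD for a 0.8 SD gap. At r = 0.5 the planned baseline covariate already removes more than half of it, and at higher r more still.

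**Step 4: power.** Take 0.5 as the effect in residual SDs of the planned model and divide it by √(1 − partial R²). Power at 128 is then 80.1% with no gain, 82.1% at a partial R² of 5%, and 84.1% at 10%. For stable gaps (at most 4.4%) it is at most about 82%.

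**The case against.** The strongest reply is that nothing here is wrong. Under randomisation, adjusting for age and baseline is valid. Omitting a further prognostic covariate brings no systematic bias, chance imbalance is already reflected in the standard error and the 5% error rate, and the sample size does not depend on covariates. All of this stands.

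A reader might infer more than the article supports, in four ways:
- *That sex is strongly related to the outcomes.* No size is given for any such relation. Sex-specific grading, a device setting and external step recommendations show that sex is relevant, but they do not show how much it predicts follow-up given baseline. The remark on knowledge is qualitative only.
- *That a chance imbalance would go uncorrected.* Baseline adjustment corrects the part of a sex gap that the baseline value carries. Only the remainder is left.
- *That body composition in boys and girls diverges enough over these ages to make the residual effect large.* The article gives the age range but no sex-specific trajectories. The 5 to 9% figure needs a gap that widens by 0.2 SD within about four months, and nothing in the article supports or excludes that.
- *That the allocation is known to be unstratified.* Section 2.4 is silent, and a condensed article may omit the detail.

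None of these replies shows a disadvantage in adding a sex main effect.

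**Conclusion.** The point holds as a free improvement of low severity. The stated model is valid, but it leaves out a variable that is already recorded and that the article itself sets beside age. The likely gain is small: about 0 to 4% of residual variance under stable sex gaps, and about 5 to 9% only if the gap widens by 0.2 SD during the study. At the 17-point imbalance, the residual shift for stable gaps of 0.5 to 0.8 SD is 2 to 12% of the planned effect (0.008/0.5 to 0.060/0.5). All of these sizes rest on the assumed sex split, gaps and correlations, since the article supplies none of them. The best reason to act is that sex can be named now at almost no cost, whereas adding it after seeing an imbalance would be open to challenge.

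**What to change.** In Section 2.8, state the adjustment as *age, sex and the baseline value of the outcome*. An age × sex term is optional: no calculation here supports requiring it, least of all for every outcome.

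The cost is a one-word addition and no new data. The between-subject residual degrees of freedom go from 128 − 4 = 124 (intercept, group, age, baseline) to 123. If the software also fits each covariate's interaction with time, sex takes one further within-subject degree of freedom when time has two post-baseline visits. The sample size need not change.
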